### Eligibility Criteria

Participants will be eligible for participation if they will be enrolled on any degree course at the beginning of the study, be able to write, read and speak Italian, and have regular access to the internet. The exclusion criteria will be the presence of ongoing severe mental disorders according to the Diagnostic and Statistical Manual of Mental Disorders (DSM–5 - American Psychiatric Association, 2013), such as major depression, bipolar disorder, psychotic disorders. Exclusion criteria will also include the presence of suicidal ideation. To evaluate the presence of ongoing clinical disorders a series of standardized questionnaire will be use. If the questionnaire suggests elevated levels of symptomatology the student will be contacted for a diagnostic interview. If severe ongoing clinical conditions (e.g., mood disorders, psychotic disorders) or suicidal ideation will be confirmed, the student will receive feedback about his symptomatology and will be directed toward an intervention that fits more with his or her needs (i.e., psychological counseling, psychotherapy). In this case, the NoiBene intervention can be used as a support for their therapy.

### Measures

#### Measures for the Assessment

To exclude the presence of any ongoing severe mental disorders, the Symptom Checklist-90-Revised (SCL-90-R; Derogatis, 1975; Italian validation by Sarno et al., 2011), the Millon Clinical Multiaxial Inventory-III (MCMI-III; Millon, 1997; Italian validation by Zennaro et al., 2008) and the Structured Clinical Interview for DSM-5 (SCID-5-CV; First et al., 2016; Italian validation by First et al., 2017) will be used to detect mental health concerns. The SCL-90-R is a self-report questionnaire used to evaluate a broad range of symptoms of psychopathology (i.e., somatization, obsessive-compulsive, interpersonal sensitivity, depression, anxiety, hostility, phobic anxiety, paranoid ideation, and psychoticism). It also evaluates an index of overall psychological distress, an index of the intensity of symptoms, and the number of self-reported symptoms. Considering the Italian version, Cronbach’s alpha ranges from 0.68 to 0.87. The MCMI-III is a self-report questionnaire that provides information about personality disorders and clinical syndromes according to the DSM-IV-TR (American Psychiatric Association, 2000). The internal consistency of the questionnaire is moderate, with Cronbach’s alpha ranging from 0.66 to 0.95. The SCID-5-CV is a semi structured interview to make major DSM-5 diagnoses (American Psychiatric Association, 2013). The percentage of positive agreement between the interview and clinical diagnoses ranges between 73 and 97% (Osório et al., 2019).

#### Primary Outcome

Primary outcomes will include changes in psychological and mental well-being evaluated with the Psychological General Well-Being Index (PGWBI - Dupuy, 1984; Italian validation by Grossi et al., 2002) and the Warwick-Edinburgh Mental Well-being Scales (WEMWBS - Tennant et al., 2007; Italian validation by Gremigni and Stewart-Brown, 2011). The PGWBI is a 22-item Health-Related Quality of Life questionnaire that evaluates self-perceived health and psychological well-being. Especially, it evaluates six dimensions: anxiety, depressed mood, positive well-being, self-control, general health and vitality. The questionnaire provides a score for each dimension and a total score, with higher scores indicating greater psychological well-being. The questionnaire demonstrated a good internal consistency with Cronbach’s alphas ranging from 0.90 to 0.94. The WEMWBS is a 14-item scale that evaluates mental well-being, covering subjective well-being and psychological functioning. The questionnaire provides a total score reflecting aspects of positive mental health. The Italian questionnaire has a good internal consistency coefficient with a Cronbach’s alpha of 0.86.

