## Abstract

University students’ mental health has become a public health issue since increasingly students report high levels of psychological distress. Mental health difficulties influence students’ lives, such as academic performance, relationships satisfaction, and quality of life. Moreover, different kinds of obstacles often hinder help-seeking behavior. Such evidence strongly suggests the need to implement prevention and promotion strategies to increase health and well-being in educational contexts. This article presents a study protocol for implementing and evaluating NoiBene, an evidence-based group intervention that aims to promote mental health and well-being, improve a series of transversal competencies (e.g., emotional awareness, commitment to values, assertiveness, goal setting), and decrease dysfunctional transdiagnostic mechanisms (i.e., perfectionism, repetitive thinking, experiential avoidance). A randomized controlled trial will be conducted to evaluate the protocol’s efficacy. Participants will be assigned to one of the three conditions: the NoiBene Group condition (NB-G), the NoiBene guided web-based condition (NB-WB), or the waiting list condition (WLC). The NB-G intervention consists of six face-to-face group meetings, each dedicated to specific issues related to well-being or vulnerabilities. Every meeting includes an explanation of the theoretical contents, individual and group exercises, and role-plays. The NB-WB intervention covers the same topic addressed in the NB-G intervention. In this case, participants carry out a series of online modules, including theoretical explanations, practical exercises, useful activities, and self-monitoring tools. Students will individually meet the Tutor once every 2 weeks. The primary outcome will include an increase in mental health and well-being. Secondary outcomes will include changes in emotional awareness, assertiveness, perfectionism, rumination, worry, self-criticism, experiential avoidance, and academic performance and satisfaction. We expect that participants in both NoiBene conditions will show these outcomes. However, we hypothesized that the NB-G conditions will be more effective than the NB-WB in improving assertiveness. Besides treatment efficacy, we expect that students can benefit from the NB-G or NB-WB differently based on their specific behavioral and motivational patterns. Outcomes will be assessed at pre-, post-intervention and 6-months follow-up. In conclusion, we believe that NoiBene is a promising tool that can improve students’ well-being, and it could have positive implications for preventing mental health disorders among students.

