## Statistical Analysis

Data will be processed using SPSS (IBM) version 27. Descriptive analysis will be run for all the sociodemographic and academic variables, on data related to the satisfaction questionnaires and on SCL-90-R and MCMI-III scores. Chi-Square tests will be used to investigate differences between participants in the three conditions on baseline demographic variables and gender variables. With the same aim, a series of Student’s *t*-test will be run on age variable and on all baseline measures. If the test will provide significant *p*-values, effect sizes will be calculated considering Cohen’s d (small > 0.20, medium > 0.50, large > 0.80). If some variables will result significantly different between conditions, they will be included as covariant in the further analysis. A series of mixed models of analysis of variance (ANOVAs) will be run to investigate the efficacy of the intervention on the PWBI, WEMWBS, TAS-20, SIB, MPS, LOSC, RRS, PSWQ, and AAQ scores, as a function of the factor between CONDITION (NB-G vs. NB-WB vs. WLC) and the factor within TIME (Baseline vs. Post-Intervention vs. Follow-Up). The level of significance was set at *p* < 0.05. Effect sizes will be calculated using partial eta squared and it will be interpreted based on benchmarks suggested by Cohen (2013): *n*^2^ = 0.01, small effect size; *n*^2^ = 0.06, medium effect size; *n*^2^ = 0.14 large effect size. The *post hoc* analyses of significant interaction will be conducted using the Bonferroni *post hoc* test.

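### Two primary scales are each tested at p < 0.05 with no either/both rule and no adjustment across them: a cheap improvement

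*Protocol article*

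**What the plan says.** The Primary Outcome section of the protocol article names two instruments in one sentence: "Primary outcomes will include changes in psychological and mental well-being evaluated with the Psychological General Well-Being Index", continued by "and the Warwick-Edinburgh Mental Well-being Scales (WEMWBS". It gives no ranking of the two.

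The Statistical Analysis section puts both in one list with seven secondary instruments: "A series of mixed models of analysis of variance (ANOVAs) will be run to investigate the efficacy of the intervention on the PWBI, WEMWBS", followed by TAS-20, SIB, MPS, LOSC, RRS, PSWQ and AAQ. (PWBI is evidently the PGWBI.) One level is given for all: "The level of significance was set at *p* < 0.05". The single multiplicity correction is tied to follow-up comparisons: "analyses of significant interaction will be conducted using the Bonferroni" procedure.

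The Participants section sizes the trial for one mixed ANOVA with three groups and three time points, at f = 0.25, 95% power and a two-sided 5% level. That gives 54 participants. Recruitment is set at about 75 to allow for attrition of around 20%.

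**The concern.** With two primary scales, each with its own test at 0.05, the reader needs to know what counts as a positive trial. Three answers are possible: either scale suffices, both are needed, or one scale leads. They have different error rates, and the article does not choose between them. As written, a significant result on one scale could be presented as evidence of efficacy on mental health and well-being while the other shows nothing. The choice could also be made after the results are known.

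The stated Bonferroni correction does not close this gap. It acts inside one ANOVA, after that ANOVA's interaction is significant, and so does not limit error across two outcomes.

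**Working it through.** **Inputs from the article.** Two primary scales, each tested at 0.05; three groups, three time points; f = 0.25; 95% power; N = 54; attrition 20%; recruitment 75.

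**Inputs assumed.** The article gives neither the correlation between repeated measures (rho), nor the nonsphericity factor (epsilon), nor the correlation between the two scales (r). The CONDITION by TIME interaction is taken as the test, because the post hoc rule is attached to it.

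**Step 1: reproduce the stated 54.** For the interaction, the noncentrality is lambda = f² × N × m / (1 − rho), with df1 = (g − 1)(m − 1) and df2 = (N − g)(m − 1). With g = 3, m = 3, rho = 0.5 and epsilon = 1:

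- N = 54: lambda = 0.0625 × 54 × 3 / 0.5 = 20.25, df = 4 and 102, power 95.8%.
- N = 51: power 94.6%, which is too low.

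So 54 is reproduced. Other values of rho give a different N (0: 102; 0.3: 72; 0.7: 33), so rho = 0.5 is used below.

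**Step 2: error if either scale counts.** For independent tests, 1 − 0.95² = 1 − 0.9025 = 9.75%. For correlated tests, two methods were used: a bivariate normal calculation, and a simulation of the two interaction F tests (18 per arm, 40,000 runs per correlation).

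| Assumed r | Bivariate normal | Simulated F tests |
|---|---|---|
| 0 | 9.75% | 9.7% |
| 0.3 | 9.5% | 9.6% |
| 0.5 | 9.1% | 9.3% |
| 0.7 | 8.3% | 8.5% |
| 0.8 | 7.8% | 7.9% |
| 0.9 | 7.0% | 7.0% |

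**Step 3: error if both scales are required.** A false claim then needs a rejection on any scale with no true effect, and each such rejection has probability 5%. The error is therefore at most 5%, whatever r is.

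**Step 4: power at 0.025 per scale,** with the Step 1 assumptions:

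- 54 completers: 92.5%.
- 60 completers: lambda = 0.0625 × 60 × 3 / 0.5 = 22.5, df = 4 and 114, power 95.3%.
- Planned recruitment: 75 × (1 − 0.20) = 60 completers.

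**Step 5: power if both are required at 0.05.** Power per scale is 95.8% at 54 and 97.5% at 60. If the tests were independent, joint power would be 0.958² = 91.8% and 0.975² = 95.1%. It is higher if they are positively correlated.

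**The case against.** The strongest defence is that the article nowhere says either scale suffices. It joins the two scales with a plain conjunction, and its hypotheses speak of mental health and well-being together. If both were required, no error would be inflated. A condensed article may also leave such a rule to a fuller document.

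Part of this stands: the either-scale reading is not established. The both-scales reading is not established either. The article also does not leave multiplicity wholly to another document: its Statistical Analysis section fixes the test, the level and the place of the correction, and puts that correction only at the post hoc stage.

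A reader might infer more than the article supports:

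- **That error is nearly twice a stated 5%.** The 9.75% is a ceiling that needs both an either-scale rule and independent tests. Two self-report well-being scales in the same students are probably positively correlated. The article also states 5% as a level for each test and for one power calculation, never as a trial-wide error rate.
- **That nine instruments at 0.05 give 37% error** (1 − 0.95⁹, independent tests). Seven of the nine are secondary, so this figure does not measure error in the main conclusion.
- **That the six PGWBI dimensions multiply the primary tests.** The sentence "The questionnaire provides a score for each dimension and a total score" describes the instrument. The analysis section lists the scale once, and nothing says the dimensions will be tested.
- **That the abstract contradicts the body.** Its wording, "The primary outcome will include an increase in mental health and well-being", names a construct that the body measures with two scales. This is loose wording.

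**Conclusion.** The point holds as a cheap improvement. Two primary scales are each tested at 0.05, with no either/both rule and no adjustment across them.

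The size depends on the missing rule. If either scale counts, the chance of at least one false-positive primary result is about 7% to 9% for correlations of 0.5 to 0.9, and cannot exceed 9.75% when the tests are independent or positively correlated. If both are required, it is at most 5%. The correlations are assumptions, since the article gives none. The absence of the rule is certain from the text; the amount of inflation is conditional.

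**What to change.** Keep the planned three-by-three mixed ANOVA and add one rule before the data are seen. Any of these will do:

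1. Apply Holm across the PGWBI total and the WEMWBS total: the smaller p against 0.025 and, if that is significant, the larger against 0.05.
2. Require both totals to be significant at 0.05.
3. Name one total as the single primary outcome and the other as the first secondary outcome.

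Add that the remaining instruments are secondary and not confirmatory. A new contrast or a different primary time point is not needed to repair multiplicity.

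The cost is a short paragraph and, under options 1 and 2, a small loss of power. On the assumptions that reproduce 54 (interaction test, rho = 0.5, epsilon = 1), 0.025 per scale has the power shown in Step 4; Holm does at least as well. The 60 completers expected from 75 recruits keep power above the protocol's 95% target, so recruitment can stay as planned.

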#### Secondary Outcomes

Secondary outcomes include changes in emotional awareness, assertiveness, repetitive thinking, perfectionism, and experiential avoidance.

##### Emotional Awareness

Emotional awareness is the ability to identify, recognize, manage, and communicate one’s and others’ emotions (Lane and Schwartz, 1987). We will assess the ability to identify, recognize and communicate emotions with the Toronto Alexithymia Scale-20 (TAS-20; Bagby et al., 1994a,b; Italian validation by Bressi et al., 1996). The TAS-20 is one of the most used measures of alexithymia and it focuses on the ability to identify and describe feelings. Indeed, the questionnaire has 3 subscales: difficulty describing feelings, difficulty identifying feelings, and externally oriented thinking. It also provides a total score for alexithymia. The Italian version demonstrated good internal consistency for the total score (α = 0.81).

##### Assertiveness

To evaluate the level of assertiveness, we will use the Scale for Interpersonal Behavior (SIB; Arrindell and Van der Ende, 1985; Italian validation by Arrindell et al., 1999), a self-report questionnaire used to measure distress in state assertiveness (distress scale), and the probability of engaging in a specific assertive behavior (performance scale). The SIB contains four dimensions for each scale: negative assertion, personal limitation, initiating assertiveness, and positive assertion. It also provides an overall measure of assertion for each scale. The Italian version has internal consistency coefficients ranging from 0.73 to 0.91.

##### Repetitive Thinking

Repetitive thinking is defined as a process of passive thinking, uncontrollable, and focused on negative content. Two forms of repetitive thinking have been mostly recognized: rumination and worry (Ehring and Watkins, 2008). To assess rumination, we will use the Ruminative Response Scale (RRS; Nolen-Hoeksma and Morrow, 1991; Italian validation by Palmieri et al., 2007), one of the most used self-reported questionnaires to measure depressive rumination. To assess worry, we will use the Penn State Worry Questionnaire (PSWQ; Meyer et al., 1990; Italian validation by Morani et al., 1999), a self-administered questionnaire that aims to measure worry regarding its occurrence, pervasiveness, and intrusiveness. The Cronbach’s alpha of the Italian version was 0.85.

##### Self-Criticism

To assess self-criticism, we will use the Level of Self-Criticism (LOSC; Thompson and Zuroff, 2004; Italian validation by Manfredi et al., 2016), a self-reported questionnaire designed to measure two dysfunctional forms of self-criticism: comparative self-criticism and internalized self-criticism. The authors reported Cronbach’s alpha coefficients of 0.81 for CSC and of 0.87 for ISC.

##### Experiential Avoidance

To assess experiential avoidance, we will use the Acceptance and Action Questionnaire-II (AAQ-II; Bond et al., 2011; Italian validation by Pennato et al., 2013), one of the most used measures of psychological inflexibility. Psychological inflexibility is defined *“the rigid dominance of psychological reactions over chosen values and contingencies in guiding action”* (Bond et al., 2011, p. 678). According to the ACT model, psychological inflexibility is the cornerstone of experiential avoidance (Pennato et al., 2013). It is a 10-item questionnaire that aims to measure psychological inflexibility, a measure of experiential avoidance. The Italian version showed good internal consistency (α = 0.83).

##### Perfectionism

Perfectionism is defined as the need to reach high personal standards, accompanied by critical self-evaluations and concerns regarding others’ evaluations and mistakes (Frost et al., 1990). We will assess perfectionism using the Multidimensional Perfectionism Scale (MPS; Frost et al., 1990; Italian validation by Lombardo, 2008), a self-reported questionnaire widely used in research and clinical settings to evaluate perfectionism. The Italian version of the questionnaire includes four scales: (1) high personal standards; (2) concern over mistakes and doubt about mistakes; (3) parental expectations and parental criticism; (4) appreciation for order and organization. Cronbach’s alphas for the four scales have been reported ranging from 0.76 to 0.87.

##### Academic Performance and Satisfaction

An *ad hoc* questionnaire will be administered to evaluate academic performance (i.e., number of taken and passed exams, mean grades, percentage of attended lessions). The questionnaire will also include self-reported information about academic satisfaction (i.e., “*I feel satisfy of my academic performance”*), perceived self-efficacy (i.e., “*I can reach my academic goals,”* “*I have a good study method,”* “*I can organize my time to study”*), and to investigate concerns about the university (i.e., “*I feel anxious during the study,”* “*I feel anxious during the exams,”* “*I can not sleep the night before the exams,”* “*I spend a lot of time worrying about university,”* “*I feel anxious to speak with my colleagues,”* “*I feel anxious to speak with my professors”).*

#### Sociodemographic Questionnaire

An *ad hoc* questionnaire will be administered to collect information about the residence, professional status, psychological past/current treatment and educational level.

#### Feedback About the Program

An *ad hoc* questionnaire will be administered to collect feedback from participants in the NB-G condition after every meeting. The questionnaire consisted of 13 items, with 10 items scored on a five-point Likert scale ranging from 1 (strongly disagree/very poor) to 5 (strongly agree/excellent), and three open answer questions. The questionnaire aims to evaluate the level of satisfaction with the contents and activities proposed during the meeting, to collect opinions about the quality of the education and the ability of the Tutor to be understandable and engaging. Lastly, the questionnaire asks for any opinions and suggestions. Only at the end of the last meeting eight additional questions are presented in the questionnaire. These questions aim to investigate the perceived utility of NoiBene and collect opinions and suggestions for future developments. See Supplementary Appendix 1 for the entire questionnaire.

At the end of the program, an *ad hoc* questionnaire will be administered to collect feedback among participants in the NB-WB condition. The questionnaire consisted of 70 questions, with 63 items scored on a five-point Likert scale ranging from 1 (strongly disagree) to 5 (strongly agree), and seven open answer questions. The questionnaire aims to investigate the intervention’s perceived utility, evaluate the level of satisfaction with the contents and activities proposed, collect opinions about the Tutor, and ask for any suggestions for future developments. See Supplementary Appendix 2 for the entire questionnaire.

#### Therapeutic and Group Relationship

To evaluate therapeutic and group relationship participants in the guided web-based and group conditions will answer an adaptation of Working Alliance Inventory for guided Internet interventions (WAI-I; Gómez Penedo et al., 2020) and the Group Questionnaire (GQ; Krogel et al., 2013; Burlingame et al., 2017; Italian validation by Giannone et al., 2020), respectively.

The WAI-I is a 12-items questionnaire scored on a 5-point Likert scale. It is used for the assessment of the therapeutic alliance in the context of guided internet-based intervention. The questionnaire provides two subscales: (1) goal and task (i.e., agreement on the goal and on the task); (2) bond (i.e., development of an affective bond). The items of the WAI-I were derived from the WAI-SR (Hatcher and Gillaspy, 2006). In the adaptation the item remained similar to the original scale, but the word “session” and “therapy” were rephrased with the word “online program,” and the word “therapist” was rephrased with the word “tutor.” The Cronbach’s α for the WAI-I total score was 0.93. Regarding the two subscales, the Cronbach’s αs were 0.93 for the task and goal agreement with program dimension and 0.89 for the bond with therapist dimension. The GQ is a 30-items questionnaire scored on a 7-point Likert scale. It provides information on the quality of the relationships in the group considering three main dimensions: (1) positive bonding (i.e., sense of belonging that the member has to the group, its members, and its leader); (2) positive working (i.e., ability of the group to agree upon treatment goals); (3) negative relationship (i.e., lack of trust and understanding). It also provides specific information about the group structure since it investigates relationships in the group (member - member, member - leader, and member - group). The original questionnaire shows a good internal consistency, with Cronbach’s alpha ranging to 0.80 to 0.92 for the three dimensions.

